## Abstract

**Background:**

Despite progress to expand access to HIV testing and treatment during pregnancy in Kenya, gaps still remain in prevention of mother-to-child transmission of HIV (PMTCT) services. This study addresses the need for effective and scalable interventions to support women throughout the continuum of care for PMTCT services in low-resource settings. Our research team has successfully implemented the HIV Infant Tracking System (HITSystem), a Web-based, system-level intervention to improve early infant diagnosis (EID) outcomes.

**Objective:**

This study will expand the scope of the HITSystem to address PMTCT services to bridge the gap between maternal and pediatric HIV services and improve outcomes. This paper describes the intervention development protocol to adapt and pilot an HITSystem version 2.0 to assess acceptability, feasibility, and preliminary PMTCT outcomes in Kenya.

**Methods:**

This is a 3-year intervention development study to adapt the current HITSystem intervention to support a range of PMTCT outcomes including appointment attendance, antiretroviral therapy (ART) adherence, hospital deliveries, and integration of maternal and pediatric HIV services in low-resource settings. The study will be conducted in 3 phases. *Phase 1* will elicit feedback from intervention users (patients and providers) to guide development and refinement of the new PMTCT components and inform optimal implementation. In *Phase 2*, we will design and develop the HITSystem 2.0 features to support key PMTCT outcomes guided by clinical content experts and findings from Phase 1. *Phase 3* will assess complete PMTCT retention (before, during, and after delivery) using a matched randomized pilot study design in 2 hospitals over 18 months. A total of N=108 HIV-positive pregnant women (n=54 per site) will be enrolled and followed from their first PMTCT appointment until infant HIV DNA Polymerase Chain Reaction testing at the target age of 6 weeks (<7 weeks) postnatal.

**Results:**

Funding for this study was received in August 2015, enrollment in Phase 1 began in March 2016, and completion of data collection is expected by May 2019.

**Conclusions:**

This protocol will extend, adapt, and pilot an HITSystem 2.0 version to improve attendance of PMTCT appointments, increase ART adherence and hospital-based deliveries, and prompt EID by 6 weeks postnatal. The HITSystem 2.0 aims to improve the integration of maternal and pediatric HIV services.

**Trial Registration:**

ClinicalTrials.gov NCT02726607; https://clinicaltrials.gov/ct2/show/NCT02726607 (Archived by WebCite at http://www.webcitation.org/78VraLrOb)

**International Registered Report Identifier (IRRID):**

DERR1-10.2196/13268

## Introduction

### Background

Despite impressive progress to expand access to HIV testing and treatment during pregnancy in Kenya [1,2], gaps still remain in achieving comprehensive prevention of mother-to-child transmission of HIV (PMTCT) services. Despite widespread access (77% to 80%) to the highly efficacious Option B+ antiretroviral therapy (ART), the current rate of perinatal transmission in Kenya is estimated at 8.3% to 11.5% [3-5]. Late and inconsistent attendance at antenatal appointments, suboptimal ART adherence during pregnancy and breastfeeding, high rates of unskilled deliveries, and high dropout throughout the PMTCT cascade are among the barriers to eliminating perinatal HIV infection in Kenya [6].

Although Kenyan national guidelines encourage 4 or more antenatal care (ANC) visits [7], an estimated 11.2% to 57.6% [8,9] attend all 4 appointments, with 95% of women attending at least 1 ANC appointment [2]. Attendance of all PMTCT appointments is crucial for monitoring treatment, progression of pregnancy, and managing risk of transmission. Poor medication adherence during pregnancy and breastfeeding compromises the efficacy of ART to prevent HIV transmission. In Kenya, approximately 15% to 20% of pregnant and postpartum women are less than 95% adherent to their ART regimen [10,11]. Since 2012, hospital deliveries are free of charge; yet, nationwide, only 61% of births are facility-based [9], with HIV positive women more likely to have a nonfacility delivery than HIV uninfected women [12]. Home deliveries among HIV positive women miss opportunities for timely infant ART prophylaxis, which can reduce the risk of perinatal transmission by up to 47% in low-resource settings [13-16]. Infants of mothers with suboptimal drug adherence are more vulnerable to perinatal HIV transmission [17,18], thus infant ART prophylaxis remains a critical safeguard.

The PMTCT cascade necessitates that women successfully navigate a series of steps including maternal HIV counseling and testing, initiation and monitoring of ART, delivery care, infant ART and cotrimoxazole prophylaxis, linkage into early infant diagnosis (EID) care for their HIV-exposed infants, and linkage to lifelong HIV care for themselves. Although HIV testing during ANC is high (93.1%) [2], rates of retention after successful linkage to PMTCT are low. In a study conducted by Ayuo et al [19], 31.9% of pregnant women enrolled in PMTCT were disengaged from care for more than 30 consecutive days (thus missing a medication refill appointment) at least once during their pregnancy, with 22.5% of all patients disengaged during the critical phase immediately before delivery. These data reflect a setting with an active outreach program for retention and thus may underestimate attrition in facilities without outreach programs. After delivery, an additional 19.3% to 45% of infants are lost to follow-up [20,21]. At least one quarter of infants are enrolled late in EID, missing the target for EID testing by 6 weeks of age [22]. Consequently, a significant proportion of mother-infant pairs receive incomplete services [23].

Mobile phone and Web-based technologies provide viable solutions to individual and system-level challenges in the delivery of HIV services in Kenya and other African countries**.** Short message service (SMS) text messaging interventions have improved attendance at ANC appointments [24,25], medication adherence and viral suppression [15,16], and postpartum PMTCT retention [26]. Tailoring health messages to the individuals within the target population increases participant retention and is critical to the success of mHealth interventions [27-29]. Most mHealth interventions for EID have focused on lab-specific efficiency [30], patient-specific adherence, or retention support [31], whereas the HIV Infant Tracking System (HITSystem) mHealth intervention was the first to link laboratory, clinical, and patient stakeholders in one integrated system [32].

This study addresses the need for effective and scalable interventions to coordinate the continuum of care for PMTCT services in low-resource settings to maximize retention and minimize infant HIV infection. Our research team has successfully implemented a Web-based mHealth intervention called the HITSystem, which utilizes available technology (internet and texting) to improve communication and accountability between EID stakeholders to optimize outcomes for HIV-exposed infants [33,34]. The HITSystem is unique as a *system-level* mHealth intervention combining SMS outreach to mothers of HIV-exposed infants and algorithm-based dashboard alerts to prompt provider (maternal and child health [MCH]/HIV and laboratory) action, and it demonstrated significant reductions in turnaround times for Polymerase Chain Reaction (PCR) test results (2.3 weeks faster), mother notification of results (1.3 weeks faster), younger infant age at ART initiation (7.6 weeks younger), and higher retention throughout the complete 18-month EID cascade of care (85% vs 60%; aOR 3.7 (2.5 to 5.5); *P*<.001) when compared with standard EID services [32]. This proposal responds to requests from hospital administrators and health care providers to expand the scope of the HITSystem to include antenatal PMTCT services and to bridge the current gap between maternal and pediatric HIV services. Thus, this intervention development protocol will adapt and pilot an HITSystem version 2.0 that prospectively tracks and supports HIV positive women through their pregnancy and delivery, linking them to EID follow-up at birth (initial HITSystem 1.0) to facilitate linked mother-infant data and retention. We will assess the acceptability, feasibility, and preliminary impact on PMTCT retention of the HITSystem 2.0 intervention.

### Study Overview

This is a 3-year intervention development study to adapt and pilot test an extension of the current HITSystem intervention to support a range of PMTCT outcomes including retention in ANC, ART adherence, hospital deliveries, and integration of maternal and pediatric HIV services in low-resource settings. The study will be conducted in 3 phases (Figure 1). *Phase 1* is designed to elicit feedback from intervention users (patients and providers) to guide development of the new PMTCT components and inform optimal implementation at the intervention site. *Phase 2* involves the technical design and development of HITSystem 2.0, a new iteration of the HITSystem to support key PMTCT outcomes (appointment attendance, ART medication adherence, hospital-based delivery, and linkage to EID). Phase 2 development will be guided by clinical content experts and findings from Phase 1. This involves close collaboration with programmers and system users to refine the interface and customize options. *Phase 3* will pilot the HITSystem 2.0 in 1 hospital over an 18-month period and compare targeted PMTCT outcomes with those at a matched control hospital.

**Figure 1 figure1:**

Study phases—an iterative process of qualitative research and HIV Infant Tracking System (HITSystem) 2.0 design, development, and refinement, which precedes the HITSystem 2.0 pilot and evaluation.

## Methods

### Phase 1: Formative Research

Phase 1 seeks to understand optimal HITSystem SMS text messaging strategies. We draw on the Information Processing Communication Theory [35-37], which identifies the conditions that encourage people to actively attend to health messages, to guide questions regarding text message content and timing. We will recruit HIV positive pregnant and postpartum women who are/were enrolled in PMTCT care at the intervention site to participate in 3 focus groups to elicit (1) strategic communication and customization of SMS text messages to motivate target behaviors while protecting confidentiality, (2) barriers to patient retention and ART adherence, and (3) strategies for mobile phone outreach and alternatives for patient follow-up. Focus groups will include n=8 women, with 2 of the 3 focus groups including HIV-positive pregnant women (second and third trimester) and the third including HIV-positive postpartum women (2 to 16 weeks), thus representing a range of gestational and postpartum periods. In addition, key informant interviews will be conducted with all staff engaged in PMTCT services (antenatal, maternity, postnatal, laboratory, pharmacy, and mentor mothers; approximately n=8) at the intervention site to strategize optimal HITSystem 2.0 implementation, given PMTCT provider capacity and existing systems for patient flow. In addition to notetaking, with participants’ consent, the focus groups and interviews will be digitally recorded. Participants will receive 500 Kenyan Shillings (approximately US $5) in appreciation of their time. The research protocol was reviewed and approved by IRB at the Kenya Medical Research Institute in Nairobi, Kenya, and the University of Kansas Medical Center. Informed consent was conducted with all participants before study engagement.

#### Analyses for Focus Group and Key Informant Interview Data

Audio files will be translated and transcribed in English, coded, and analyzed. In total, 2 study team members will independently code data for a priori (preferences for health messaging, potential barriers to retention and ART adherence, alternative strategies for patient follow-up, and provider recommendations for optimal implementation) and emergent themes. Through consensus, we will develop a codebook with typical exemplars for each theme, noting the frequency and distribution of themes within the larger topic areas. Summarized themes will directly inform HITSystem 2.0 development in Phase 2.

### Phase 2: Intervention Development

HITSystem 1.0 is currently in use in multiple health facilities in Kenya. The primary goals of the HITSystem 1.0 are to (1) improve EID and clinical management of HIV-exposed infants and (2) facilitate early ART initiation for HIV positive infants [33,34,38,39]. The HITSystem is accessed on the Web using a computer or tablet, with mobile broadband modems that respond to a cellular signal. The primary components include (1) provider alerts to complete time-sensitive interventions, (2) real-time communication of PCR laboratory results to hospitals to reduce turnaround time, (3) persistent follow-up for timely ART initiation among HIV-positive infants, and (4) retention in EID care via SMS text messaging and/or patient tracing.

The HITSystem 2.0 intervention will (1) utilize electronic prompts to notify PMTCT providers and program managers when action is required to support timely services, patient retention and adherence, and linkage to EID once infants are born [33,34] and (2) send SMS text messages to HIV-positive pregnant women’s mobile phones with the aim to motivate adherence to medication, remind women of ANC appointments and medication refills, and prompt preparation for a hospital delivery.

#### HIV Infant Tracking System 2.0 Intervention Specifications

Clear reporting of intervention components and implementation strategies is needed for meaningful application in practice or testing in research [40,41]. The entry point into the HITSystem 2.0 will be the first PMTCT appointment for women previously diagnosed with HIV or newly confirmed HIV positive during antenatal HIV screening. Actions include automated prompts to PMTCT providers, prompts to central laboratory technicians who process viral load (VL) samples, and SMS texts to patients driven by national algorithms for optimal PMTCT care (Table 1). Automated electronic prompts to providers will persist as Web-based dashboard alerts until addressed. Automated SMS texts are sent to HIV-positive pregnant women as cues to action; women can select the preferred content and frequency for one-way ART adherence text messages at the time of enrollment. This is one of the first interventions to target adherence support messages during pregnancy, thus texting options (content and frequency) will be informed by Phase 1 formative research, and actual preferences will be assessed by this pilot study. Community health care workers can reach out to patients who miss services and/or do not respond to SMS text messages or calls to encourage retention. The HITSystem 2.0 will integrate PMTCT and EID services through 1 coordinated system-level intervention; this will permit longitudinal follow-up of mother-infant pairs to assess PMTCT outcomes.

**Table 1 table1:** HITSystem 2.0 intervention components. Expected timing, dose, and target of alerts and SMS (short message service) texts to providers and HIV positive pregnant women.

Actors	Actions	Timing	Dose^a^	Target
Hospital-based providers; providers	Algorithm-driven electronic alerts	When PMTCT^b^ service late/missing (enrollment-infant EID^c^ link)	Avg=8 per mom, range=0 to 14+	PMTCT quality: complete PMTCT retention (pregnancy to EID link)
Lab-based providers; lab techs	Algorithm-driven electronic alerts	When receipt of VL^d^ sample or VL results delayed	Avg=1 per mom, range=0-2+	PMTCT efficiency: reduced turn-around time for key PMTCT services
HIV-positive pregnant women	Algorithm-driven electronic SMS text messages	Appointment reminders (2 days before appointment); adherence reminders (daily, weekly, biweekly, monthly); facility-based delivery reminders (4 and 2 weeks before EDD^e^)	Avg=4 per mom, range=0-8+; avg=20 per mom, range=0-245+; avg=2 per mom, range=2 to 2	PMTCT quality and PMTCT efficiency

^a^Dose represents anticipated study averages and ranges only, assuming one alert per alert type per pregnancy. Actual dose will depend on client-specific factors such as gestational age at enrollment, adherence to PMTCT guidelines and scheduled services, and frequency preferences for adherence reminders.

^b^PMTCT: prevention of mother-to-child transmission of HIV.

^c^EID: early infant diagnosis.

^d^VL: viral load.

^e^EDD: estimated due date.

#### Process for Phase 2 Development

We will employ the 4D’s process to define, design, develop, and deploy the intervention [42]. The clinical algorithms and portions of the system development will be designed before completion of Phase 1, but focus group and interview findings will customize and refine critical aspects of the 4D’s process, incorporating input from Kenya’s current PMTCT treatment guidelines and user feedback regarding strategic messaging, patient and provider barriers, and strategic implementation. The iterative process of Phases 1 and 2 will enhance the design and development by ensuring a user-friendly, robust, interactive, and secure software system to increase engagement, retention, and quality PMTCT outcomes.

### Phase 3: Trial Intervention

#### Trial Design

We will employ a matched, randomized pilot study design in 2 government hospitals with comparable resources, patient volume, and basic patient characteristics. One hospital will be randomized to receive the HITSystem 2.0 intervention and the other hospital will maintain standard of care PMTCT services. An extended 18-month implementation period will allow 9 months to reach the sample size requirement of n=54 at each hospital and another 9 months to ensure complete prospective outcome data from the first PMTCT appointment in pregnancy until the infant’s first HIV DNA PCR test result is determined. This follow-up period will assess complete retention throughout PMTCT services, ART adherence, and rates of infant HIV transmission. We will also collect retrospective PMTCT outcome data from each hospital for the 18 months before implementation to facilitate pre- and postcomparisons at the same facility.

Satisfaction interviews with HITSystem 2.0 users (HIV positive women and providers) will inform barriers to use that can be targeted either through future strategic refinement of the design or collaboration with key partners to address constraints beyond the scope of this intervention.

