#### Study Sites and Setting

This study will be conducted in 2 government hospitals with similar provider-patient ratios and staffing structure, Kapsabet Hospital and Bungoma Hospital, both in western Kenya. Eligibility criteria for these hospitals include government funding; the current provision of PMTCT, EID, and ART services; at least one dedicated provider managing PMTCT services; and maintenance of individual-level patient files. Kapsabet Hospital serves a catchment area of approximately 91,000 people [43], has an average monthly EID volume of 10, and an average infant HIV transmission rate of 2.7% [44]. Bungoma Hospital serves a catchment area of approximately 92,412 people [43], has an average monthly EID volume of 18, and an average infant HIV transmission rate of 4.2% [44]. These hospitals serve less transient local populations, making them ideal pilot sites to adapt and modify the HITSystem 2.0 for the primary outcome of complete PMTCT retention.

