#### Randomization

As a system-level intervention, it is neither feasible nor acceptable to randomize participation at the individual level. The hospital to receive the intervention will be determined by random assignment at the beginning of the study, using a random number generator program. The principal investigator and research staff will be blind to the process of assigning the sites.

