#### Power and Sample Size

The required sample size was calculated to compare differences in proportions of complete PMTCT retention for the intervention (p1) and control (p2). We estimated complete retention by combining available retention data from Kenya for each phase: antenatal retention (68%) [19], hospital-based deliveries (61%) [36], and postnatal retention for HIV-exposed infants within 12 weeks (54.9% [21] to 80.7% [20]; average 67%). Recognizing that these estimates do not represent cumulative risk for the same individuals, we conservatively estimate complete PMTCT at the control site to be 20%. Our EID pilot data showed that retention doubled at 9 months with retention rates as high as 94.2% [33]. Using a midrange between differences achieved from published studies and our own pilot study, we conservatively estimate complete retention of 47% for HITSystem 2.0 participants. A sample size of 108 (54 intervention and 54 control participants) is needed to achieve 80% power to detect a significant difference in the proportion of complete PMTCT retention with chi-square tests (goodness of fit test: contingency table) with an effect size of 0.27 and a 2-tailed alpha of .05. Accounting for the proportion with mobile phone utilization, and 1.5% maternal mortality [45] and 3.7% [46] perinatal mortality, we estimate n=70 eligible participants. During Phase 3 enrollment, we plan to enroll n=54 of the n=70 eligible PMTCT patients per hospital. On the basis of our initial HITSystem pilot where <1% of women declined, we anticipate high participation.

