#### Statistical Analyses

To examine the baseline participant and facility characteristics, we will calculate descriptive statistics including proportions for categorical variables and means (SD) or median (interquartile range) for continuous variables [47]. For the primary outcome, chi-square tests will be used to compare the proportion with complete PMTCT retention between groups [48]. We will explore correlations between complete PMTCT retention and possible predictors (eg, knowledge, motivation to complete care, maternal HIV disclosure, perceived benefit of ART, maternal depression, and risk of intimate partner violence) using Phi, point-biserial, or Spearman rho statistics depending on the measurement level of each predictor [49]. Analytic models will control for significantly different preintervention covariates across conditions and hospitals, clustered observations (eg, time nested within setting), and gestational age as it impacts the eligible/recommended number of appointments or services.

For secondary analyses, Kaplan-Meier curves will illustrate differences in the duration of PMTCT retention before, during, and after delivery, accounting for the woman’s eligible period of engagement (based on the timing of enrollment and accounting for premature infant or maternal mortality). We will then identify time periods when meaningful decreases in PMTCT retention occur, using Cox proportional-hazard regression for survival analyses (ie, retention), if all assumptions are met [50]. Known variables associated with HIV service retention (age, disclosure status, educational level, and number of children [22,51,52]) and those correlated (*P*<.10) will then be included in a generalized linear mixed model to identify a parsimonious list of predictors.

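### With one hospital per arm, the stated 80% power and the primary chi-square describe a difference between two hospitals; they describe an intervention effect only if retention would otherwise have been equal

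*Protocol article*

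**What the plan says.** The Trial Design section allocates at hospital level: "One hospital will be randomized to receive the HITSystem 2.0 intervention and the other hospital will maintain standard of care PMTCT services". The Randomization section gives the reason: "As a system-level intervention, it is neither feasible nor acceptable to randomize participation at the individual level".

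Power and Sample Size works with women as the unit. For the control site, "we conservatively estimate complete PMTCT at the control site to be 20"%; for the other, "we conservatively estimate complete retention of 47% for HITSystem 2.0 participants". From these, "A sample size of 108 (54 intervention and 54 control participants) is needed to achieve 80% power to detect a significant difference", with a chi-square test at two-tailed alpha .05. No ICC or design effect appears.

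Statistical Analyses names the primary test: "For the primary outcome, chi-square tests will be used to compare the proportion with complete PMTCT retention between groups". It adds that models will adjust for baseline covariates that differ across conditions and hospitals, for gestational age, and for "clustered observations (eg, time nested within setting").

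Trial Design also plans to collect retrospective outcome data from both hospitals for the 18 months before implementation, for before-and-after comparison within each facility. Neither the power calculation nor the primary test uses these data.

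The limitations in the Discussion cover uptake, unequal data capture and changing technology. They do not say that hospital and arm coincide.

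**The concern.** Two units are randomised, but the sample size and primary test treat 108 women as if they were the independent units. In the between-arm comparison after implementation, anything that makes one hospital retain women better than the other enters the estimated effect: staffing, local practice, access, record keeping. Randomising which of the two hospitals receives the system does not help, because one allocation cannot balance hospital characteristics.

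At stake is the meaning of the primary result. A two-sided error rate of 5% for the claim that HITSystem 2.0 changes retention requires that the hospitals would have had the same retention without it. If they would not, a significant chi-square can arise with no intervention effect, and the stated power is not power for that effect. The result is meant to inform a larger efficacy trial, so the distinction matters even in a pilot.

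**Working it through.** **Inputs from the protocol.** Retention 20% (control) and 47% (intervention), difference 0.27; 54 women per hospital; two-sided alpha .05; one hospital per arm.

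**Inputs assumed.** The ICC and the pre-existing retention gap. The protocol gives neither.

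**1. Reproduce the stated sample size.** Mean proportion (0.47 + 0.20)/2 = 0.335.

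- Uncorrected: n = [1.96·√(2·0.335·0.665) + 0.842·√(0.47·0.53 + 0.20·0.80)]² / 0.27² = 46.8, so 47 per arm.
- With continuity correction: (46.8/4)·[1 + √(1 + 4/(46.8·0.27))]² = 53.9, so 54 per arm and 108 in total. This matches the protocol.
- As a second route, a one-degree-of-freedom chi-square with standardised effect 0.27 and N = 108 has 80.1% power.

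Both routes treat the women as independent (design effect 1).

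**2. Baseline for the power comparison.** At 54 per arm the uncorrected formula gives SE₀ = √(0.335·0.665·2/54) = 0.0908 and SE₁ = √(0.4091/54) = 0.0870. Power is Φ[(0.27 − 1.96·0.0908)/0.0870] = 85.5%. Step 5 starts from this figure, not from the stated 80%.

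**3. Degrees of freedom for between-hospital variation.** 2 arms × (1 hospital − 1) = 0. The between-arm comparison cannot estimate that variation.

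**4. Fixed pre-existing gap, no intervention effect.** Exact enumeration of the uncorrected chi-square with 54 per hospital:

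| Retention at the two hospitals | Proportion of trials with p < .05 |
|---|---|
| 20% vs 20% | 5.1% |
| 20% vs 25% | 9.5% |
| 20% vs 30% | 22.2% |
| 20% vs 35% | 41.4% |

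**5. Random hospital variation, assumed ICC.** Design effect DE = 1 + (54 − 1)·ICC. Type I error of the planned test = 2·[1 − Φ(1.96/√DE)]. Power is the formula in step 2 with both standard errors multiplied by √DE, that is, for a test that knows the ICC.

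| ICC | DE | Effective n per arm | Type I error | Power |
|---|---|---|---|---|
| 0 | 1.00 | 54 | 5% | 85.5% |
| 0.01 | 1.53 | 35.3 | 11.3% | 67.8% |
| 0.02 | 2.06 | 26.2 | 17.2% | 54.6% |
| 0.05 | 3.65 | 14.8 | 30.5% | 33.7% |

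Exact enumeration with beta-distributed hospital rates (mean 20%) gives type I errors of 11.4%, 17.4% and 31.2% for the three non-zero ICCs, in line with the approximation.

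**The case against.** The strongest reply has four parts.

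*The retrospective data.* A reader might infer that the adjustment for clustering cannot be carried out at all and should be deleted. The protocol does not support that. With 18 months of earlier data from each hospital, the intervention hospital is observed both without and with the system, so hospital and condition do not coincide across the two periods. A hospital effect and a hospital-by-period contrast are then estimable, and modelling time within setting has a workable meaning. This part stands. Its limits are that the contrast removes a stable hospital gap but not changes over time specific to one hospital, and that the protocol does not attach these data to the primary test.

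*The evidence that the sites differ.* One hospital "has an average monthly EID volume of 18, and an average infant HIV transmission rate of 4.2"%, against 10 per month and 2.7% at the other. It is tempting to read this as proof of unequal retention. It is not: volume and transmission are not retention, and the transmission rates come without denominators. The protocol also reports matching on resources, staffing and patient characteristics, with catchments of about 91,000 and 92,412. Matching makes equality more plausible but does not secure it.

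*The pilot framing.* The objective speaks of acceptability, feasibility and preliminary outcomes, and efficacy is deferred to a later trial. A reader might infer that the protocol promises an efficacy conclusion from the chi-square; no section says so. But the pilot label does not alter what the stated 80% power and .05 level refer to.

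*An analysis plan that is not shown.* Model detail may sit there. The primary test and its power, however, are fixed in this document.

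**Conclusion.** The point holds for the between-arm comparison after implementation. The arithmetic behind 108 is sound, but it answers whether these two hospitals differ. It gives 80% power and a 5% error rate for an intervention effect only if the hospitals would have had equal retention without it, and the protocol does not state that condition.

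The size of the problem is illustrative because it rests on assumed values. With no intervention effect, gaps of 10 and 15 points give false positives in about 22% and 41% of trials. ICCs of 0.01 to 0.05 give type I error of about 11% to 30%, and power of about 68% and 34%, against about 85% from the same formula without clustering. These power figures should not be set directly against the stated 80%, which matches a continuity-corrected calculation, and they suppose a known ICC that this comparison cannot supply.

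**What to change.** - **Power and Sample Size.** Restate the 80% as power to detect a difference between these two hospitals, and say that it is power for an intervention effect only if there is no other between-hospital difference. Show the results for the assumed ICC range, labelled as illustration.
- **Statistical Analyses, primary outcome.** Report a risk difference with 95% CI as a two-hospital contrast. State that between-hospital variance is not estimable from the between-arm comparison, and do not use the p-value to claim efficacy.
- **Statistical Analyses, models.** Keep the modelling of time within setting, but tie it to the 18-month retrospective data. Prespecify a hospital-by-period (difference-in-differences) contrast for those retention components that are available in both periods. Note that it removes a stable hospital gap but not hospital-specific changes over time.
- **Discussion.** Add the confounding of hospital with arm to the limitations.

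The cost is a less favourable power statement and a modest amount of extra analysis. No further participants are needed, and the retrospective data collection is already planned.
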